## Abstract

**Background:**

Recurrent cardiovascular event remains high in stable coronary artery disease (SCAD), especially in patients with multiple risk factors, despite a high rate of use conventional treatment. Traditional Chinese Medicine (TCM) is a promising complementary and alternative medicine for treating SCAD, while evidence for its effect on long-term survival is limited. This study was designed to test if Chinese herbal medicine in addition to conventional treatment is more effective than conventional treatment alone in reducing major adverse cardiac event (MACE) for SCAD patients with multiple risk factors during a 1-year follow-up.

**Methods:**

This is a multicenter, placebo-controlled, double-blinded, randomized controlled clinical trial. A total of 1500 patients are randomized in a 1:1 ratio to receive the Qing-Xin-Jie-Yu Granules (QXJYG) or the placebo granules, twice daily for 6 months. The primary outcome is the combined outcomes including cardiac death, nonfatal myocardial infarction and revascularization. The secondary outcome is the combined outcomes including all-cause mortality, re-admission for acute coronary syndrome (ACS), heart failure, malignant supraventricular and ventricular arrhythmia influencing hemodynamics, ischemic stroke, and other thromboembolic events during 1-year follow-up. The assessment is performed at baseline (before randomization), 1, 3, 6, 9, and 12 months after randomization.

**Discussion:**

This is the first multicenter trial sponsored by the national funding of China to evaluate TCM in combination with conventional treatment on 1-year survival in high-risk SCAD patients. If successful, it will provide an evidence-based complementary therapeutic approach for reducing MACE from SCAD.

**Trial registration:**

The trial was registered in the Chinese Clinical Trial Registry on December 28, 2013. The registration number is ChiCTR-TRC-13004370.

**Electronic supplementary material:**

The online version of this article (doi:10.1186/s13063-016-1569-9) contains supplementary material, which is available to authorized users.

## Background

Over the past three decades, preventive and therapeutic agents have substantially improved the prognosis of stable coronary artery disease (SCAD), however, cardiovascular event remains high, especially in high-risk patients with additional multiple risk factors, such as hypertension, hyperlipidemia and diabetes mellitus, despite a high rate of use conventional treatment including aspirin, statins, β-blockers and renin-angiotensin-aldosterone system blockers, etc. [1]. In addition, increasing evidence supports a vital role of inflammation in the clinical instability of SCAD [2]. C-reactive protein (CRP), a systemic inflammatory marker, adds prognostic information to the cluster of traditional risk factors [3]. However, the novel anti-inflammatory drugs did not show a positive effect on further reducing major adverse cardiac event (MACE) [4, 5]. Therefore, it is necessary to seek more effective strategies for inhibiting inflammation and thus reducing the occurrence of MACE from SCAD.

Traditional Chinese Medicine (TCM) has been used to treat CAD for thousands of years. A meta-analysis of 70 randomized clinical trials including 9706 cases of CAD demonstrated a beneficial effect of TCM on clinical symptoms (odds ratio, 3.06 [95 % CI, 2.58 to 3.62]; *P* < 0.00001) and electrocardiograph (odds ratio, 2.46 [95 % CI, 2.16 to 2.80]; *P* < 0.00001) compared with isosorbide dinitrate, and no serious adverse effects were reported [6]. However, another systematic review pointed out that the majority of randomized controlled trials on CAD with TCM are of “poor quality”, thus more powerful evidence from high-quality clinical trials are needed for future clinical practice [7].

Qing-Xin-Jie-Yu Granules (QXJYG) have been used to treat CAD for nearly two decades in mainland China, and previous small-sample studies have demonstrated that QXJYG relieved angina pectoris and decreased cholesterol of patients with CAD [8]. QXJYG consist of five herbal granules, including *Astragalus membranaceus* (Huangqi), *Salvia miltiorrhiza Bunge* (Danshen), *Ligusticum chuanxiong Hort* (Chuanxiong), *Agastache rugosus* (Huoxiang), and *Coptis chinensis* (Huanglian). The pharmacological studies suggested that the bioactive component or structural modification of extracts from Huangqi [9], Danshen [10], and Chuanxiong [11] had effects on cardiac protection, plaque stabilization, inhibition of platelet aggregation, etc., and these three Chinese herbs are also widely used in TCM for treating CAD [12–14]. Moreover, extracts from Danshen and Huanglian exert anti-inflammatory effects [15, 16], and clinical studies showed that they decreased the level of high-sensitivity CRP (hs-CRP) in patients with cardiovascular disease [17, 18].

Therefore, QXJYG is worth investigating in high-risk SCAD patients due to the pleiotropic effect. The assumption is made that QXJYG in addition to conventional treatment may be superior to reduce inflammation of atherosclerosis and finally lead to the reduction of MACE in high-risk SCAD patients. If successful, it will provide an evidence-based complementary therapeutic approach for inhibiting inflammation and reducing MACE from SCAD.

## Methods/design

### Study objectives

This study is designed as a multicenter, double-blind, randomized, placebo-controlled, parallel-group, superiority trial to test the hypothesis that QXJYG in addition to conventional treatment is more effective than conventional treatment alone in reducing MACE, which is defined as cardiac death, nonfatal myocardial infarction and revascularization, for SCAD patients with two or more atherogenic risk factors during 1-year follow-up (see Fig. 1).

**Fig. 1 Fig1:**
[figure not shown]
Study flow of the QUEST Trial

### Design overview

The rigorous design, organization, and conduct of the trial are supervised by a Steering Committee, which comprises two members from each participating center in addition to the chairman, scientific coordinator and statistician. Eighteen clinical centers in mainland China will participate in the trial, including Xiyuan Hospital of China Academy of Chinese Medical Sciences, China-Japan Friendship Hospital, The First Hospital of Tianjin University of Traditional Chinese Medicine, etc. Data management and statistical analyses will be performed solely by data handlers and data analysts at Beijing Jiaotong University. This study follows the international recommendations for interventional trials [19]. (See the SPIRIT checklist in Additional file 1). All patients must personally sign and date an informed consent document before randomization.

### Inclusion criteria

The trial will recruit patients of both genders aged 18–75 years with evidence of CAD documented by previous myocardial infarction (>3 months before screening), percutaneous coronary revascularization (>1 month before screening), angiographic or cardiac computed tomography angiographic evidence of ≥50 % stenosis of ≥1 major coronary artery. Also required are two or more of the following four risks: a serum hs-CRP level ≥3 mg/L, a history of hypertension, hyperlipidemia, and diabetes mellitus.

### Exclusion criteria

The exclusion criteria are as follows:Combined with congenital or rheumatic heart disease or severe heart failure;Uncontrolled severe arrhythmia (including paroxysmal ventricular tachycardia and supraventricular arrhythmia), which can cause hemodynamic responses;Acute cerebrovascular disease;Uncontrolled blood pressure, with a systolic blood pressure ≥160 mmHg or a diastolic blood pressure ≥100 mmHg;Severe primary hepatic, renal, hematologic or mental disorders;Major head, chest or abdominal surgery within 4 weeks or bleeding tendency;Pregnant or lactating women;Suspected to be allergic to Chinese herbal medicine;Currently participating in another clinical trial.

### Recruitment

Inpatients and outpatients with SCAD in each center will be screened. Each potentially eligible patient will be assessed by an attending physician for whether the patient should be recruited. The aim, procedures, and possible side effects of the study granules will be explained in detail to the patients; all patients will be asked to sign a written informed consent form before randomization. Neither financial nor nonfinancial incentives will be provided to attending physicians and patients for enrolment.

### Randomization and treatment assignment

Patients are randomized in a 1:1 ratio through a centrally controlled, computer-generated, site-stratified, block randomization schedule. The study granules are labeled with serial numbers, and each patient will be assigned the lowest number available at each participating center. All patients, care providers, attending physicians, laboratory staff and biostatisticians are blind to treatment assignment until the database has been locked. Randomization started on October, 2014. Enrolment of 1500 patients is expected to be completed in August 2016.

### Interventions

Eligible patients will be allocated to receive QXJYG or placebo for 6 successive months, in addition to conventional treatment including antiplatelet, lipid-lowing, antihypertensive or antidiabetic therapy, etc., according to the guidelines [20]. The QXJYG and placebo granules were produced and packed in a single batch (Production batch number:1405001H) by China Resources Sanjiu Medical and Pharmaceutical Co., Ltd., Shenzhen, China., which has no conflict of interest relevant to this study. The test results of drug quality were consistent with the Chinese Medicine Standards of the State Food and Drug Administration (SFDA). The placebo granules are composed of 10 % crude drug of QXJYG and 90 % starch, which have the identical appearance, smell, and scent as the active treatment granules. Patients will be instructed to dissolve the granules in 150 mL hot water and take orally twice daily for 6 successive months. Any other Chinese herbal decoction or Chinese patent medicine for treating CAD is prohibited during the study.

### Outcomes

The combined primary outcomes include cardiac death, nonfatal myocardial infarction, and revascularization. The combined secondary outcomes include all-cause mortality, re-admission for acute coronary syndrome (ACS), heart failure, malignant supraventricular and ventricular arrhythmia influencing hemodynamics, ischemic stroke, and other thromboembolic events during 1-year follow-up.

Hs-CRP, blood lipids, platelet aggregation rate, echocardiography, electrocardiogram, and Seattle Angina Questionnaire (SAQ) will also be monitored periodically.

### Safety assessment

Safety will be monitored up to 6 months after intervention and evaluated based on the incidence of adverse events (AEs) including clinically significant changes in physical examinations, vital signs, and standard clinical laboratory tests (complete blood count, blood biochemical examination, coagulation [including prothrombin time (PT), thrombin time (TT), international normalized ratio (INR), activated partial thromboplastin time (APTT), and fibrinogen] and urinalysis). The National Cancer Institute’s Common Terminology Criteria for Adverse Events (CTCAE) v4.0 grading system was used to classify the nature and severity of the AEs [21].

### Follow-up

The follow-up for all patients will be scheduled at 1, 3, 6, 9, and 12 months (see Additional file 2). The primary and secondary outcomes as well as safety will be evaluated at each follow-up. If severe adverse events (SAEs) occur, the attending physician must report to the principal investigator and ethics committee immediately, who will decide whether or not to continue the treatment. Patients are also free to continue or discontinue the study at any time during the trial. Additionally, any medication change and events leading to therapy interruption will be recorded on the case record form (CRF).

### Compliance

A mobile application will be used to remind the patients automatically at each follow-up appointment. In addition, each patient will be asked to offer at least two telephone numbers in order to be contacted in time. Furthermore, attending physicians will be responsible for each patient’s questions.

To assess medication adherence, patients will be asked to return the unused granules. Unused granules accounting for more than 20 % of the total granules will be defined as nonadherence. The reasons for nonadherence (e.g., discontinuation of intervention owing to harm or unsatisfactory efficacy) will be recorded on the CRF.

### Sample size

The sample size was calculated based on the expected reduction of incidence in MACE from pre- to post-treatment at 1 year. A previous study suggested that the MACE (death, myocardial infarction, and urgent revascularization) incidence in high-risk patients with SCAD is about 10 % within 1 year [1]. Assuming a MACE incidence reduction to 7 % following treatment with QXJYG added, and given a type I error rate of alpha = 0.05, a power of 80 % (type II error rate of beta = 0.2), the sample size for one arm needed to be 630, resulting in *n* = 2 × 630 = 1260 patients. Considering a dropout rate of 20 %, a total of 1512 patients needed to be allocated to reach the required number of patients for the efficacy analysis. For convenience of randomization, we decided to recruit 1500 patients.

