For all analyses, a value of *P* < 0.05 is considered statistically significant, and all tests are two-tailed. *P* values will be reported to four decimal places. All analyses will be conducted using R software version 2.15.1 (http://www.R-project.org/), unless otherwise noted.

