### Trial status

The trial has currently recruited 1202 patients since October 2014, of which 906 have completed the 6-month follow-up. Thirty patients experienced MACE, but their allocated group is still bind. No SAEs have occurred to date.

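### The 10% planning rate comes from a different composite, and the trial's own blinded count suggests, without proving, a pooled 12-month rate below the planned 8.5%

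*Protocol article*

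**What the plan says.** Under Sample size, the protocol article cites a previous study: "MACE (death, myocardial infarction, and urgent revascularization) incidence in high-risk patients with SCAD is about" 10% within one year. It continues "Assuming a MACE incidence reduction to 7"% with the study granules added, "given a type I error rate of alpha" = 0.05 and 80% power, and concludes that "the sample size for one arm needed to be 630". That makes 1,260 patients, raised to 1,512 for 20% dropout and set at 1,500.

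The Outcomes section defines the endpoint that will be analysed: "The combined primary outcomes include cardiac death, nonfatal myocardial infarction, and revascularization". Study objectives and the abstract give the same three components. Under Statistical approach, event outcomes are compared by log-rank test and Cox model, and "all tests are two-tailed".

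Trial status reports: "The trial has currently recruited 1202 patients since October 2014, of which 906 have completed the 6-month follow-up". It adds that thirty patients have had MACE, with allocation still blinded, and that there have been no SAEs so far. The article does not compare the thirty events with the planning rates.

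**The concern.** There are two separate issues with the input rate.

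- **The composite differs.** The 10% belongs to a composite that counts death and only urgent revascularization. The trial counts cardiac death and revascularization without the urgency limit. The rate was carried over as if the two endpoints were the same.
- **The trial has its own evidence on the rate.** The thirty pooled events can be set against the planned pooled rate without unblinding, and they look low.

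The power of a log-rank or Cox comparison depends on the number of events. If the pooled rate is lower than planned, 1,500 patients yield fewer events and the trial can reliably detect only a larger effect than the one assumed. A neutral result could then be read as evidence of no benefit when the trial had little chance of showing the planned benefit.

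**Working it through.** **Inputs from the article.** Rates 10% and 7%, alpha 0.05, 80% power, 630 per arm, 1,500 recruited (Sample size); two-tailed tests (Statistical approach); "Patients are randomized in a 1:1 ratio" (Randomization and treatment assignment); 1,202 recruited, 906 past 6 months, 30 MACE (Trial status).

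**1. The plan's own figure.** Comparing 10% with 7%, two-sided 0.05 and 80% power, needs 1,356 per arm. A one-sided test needs 1,068. The log-rank form (Schoenfeld) needs 226 events, about 1,329 per arm. None of these gives 630. This is a separate error, but it sets the baseline for what follows.

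**2. Planned pooled rate and hazard ratio.** (10% + 7%)/2 = 8.5%. HR = ln(0.93)/ln(0.90) = 0.689.

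**3. Blinded rate.** 12-month risk = 1 − exp(−30/PY), assuming a constant hazard. The exact Poisson 95% limits for 30 events are 20.24 and 42.83. The number expected at 8.5% is −ln(0.915) × PY.

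| Exposure | PY | 12-month risk (95% CI) | Expected at 8.5% | P(30 or fewer) |
|---|---|---|---|---|
| 906 × 0.5, nothing for the other 296 | 453 | 6.4% (4.4% to 9.0%) | 40.2 | 0.057 |
| plus 296 × 0.25 (assumed) | 527 | 5.5% (3.8% to 7.8%) | 46.8 | 0.006 |

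More follow-up lowers the estimate further. For example, if the 906 average 9 months and the 296 average 3 months (both assumed), exposure is 906 × 0.75 + 74 = 753.5 PY and the risk is 3.9%.

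**4. Power with 1,500 patients and no dropout.** Events D = 1,500 × pooled risk. Power = Φ(√(D/4) × |ln 0.689| − 1.96). Detectable HR at 80% power = exp(−2 × (1.96 + 0.84)/√D).

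| Pooled risk | Events D | Power for HR 0.69 | HR detectable with 80% power |
|---|---|---|---|
| 8.5% (planned) | about 128 | 56% (55% comparing proportions, 750 per arm) | 0.61 |
| 6.4% | about 96 | 45% | 0.56 |
| 5.5% | about 83 | 40% | 0.54 |

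The fall from 80% to about 55% comes from the arithmetic in step 1. The lower event rate accounts for the further fall, roughly 10 points at 6.4% and 15 at 5.5%. Dropout would reduce power further.

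**The case against.** Several points on the other side stand.

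- **6.4% is not an upper bound.** It is a point estimate, and its interval reaches 9.0%. A reader might infer that the trial's data contradict the plan. On the only exposure that Trial status supports they do not: P = 0.057. The stronger result (P = 0.006) rests on assumed follow-up.
- **453 patient-years is not a strict floor.** Patients stop contributing time at their first event. If all thirty were among the 906 and had events at once, exposure would be (906 − 30) × 0.5 = 438 PY and the risk 1 − exp(−30/438) = 6.6%. The effect is small.
- **The count itself is uncertain.** Thirty MACE are reported next to a statement that no SAEs have occurred, although cardiac death, infarction and revascularization make up the MACE definition. Trial status gives no cut-off date and does not restate the definition. The hazard may also change after study treatment ends at 6 months.
- **The composite mismatch has no known direction.** Cardiac death is narrower than death, while any revascularization is broader than urgent revascularization. A reader might infer that 10% was therefore too high; the text does not show that. It also says only death, so a reading of death from any cause would need the cited study.
- **Later data do not make a prospective assumption wrong.** The 10% and 7% were the basis for the target when it was set, and that record should stay.

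None of this removes the mismatch or restores the stated power. It limits how firmly the lower rate can be asserted.

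**Conclusion.** The concern holds in a limited form. The planning rate belongs to a composite that differs from the primary outcome in two components, with no adjustment and an error of unknown direction. The blinded count points to a pooled 12-month rate below 8.5%: 6.4% on the follow-up that is documented, where 8.5% remains compatible, and 5.5% or less if the remaining recruits contributed as assumed.

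If the lower rates are right, power for the planned effect is about 45% or 40%, against about 55% at the planned rates. It would be wrong to attribute the whole shortfall from 80% to the event rate, because most of it comes from the sample-size arithmetic.

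The conclusion assumes a constant hazard, complete event reporting, the trial's own MACE definition behind the count of thirty, and no dropout in the power figures.

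**What to change.** While allocation is still blinded, have the data centre verify the pooled MACE count and person-time against the trial's own definition, and reconcile the count with the statement that no SAEs have occurred. Then add a dated addendum to the Sample size section that:

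- keeps the 10% and 7% rationale as the prospective basis;
- notes that the source study used a different composite and that the direction of the difference is unknown;
- states the verified pooled rate with its interval, and the number of events expected at 12 months;
- gives the power for HR 0.69 at that number and the HR detectable with 80% power.

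The cost is one blinded count and one added paragraph. The downside is that the stated power becomes less favourable. No unblinding or extra enrolment is needed.

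### The stated 630 per arm gives about 48% power, not 80%, for 10% versus 7% in a two-sided two-arm comparison; about 1,356 per arm would be needed

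*Protocol article*

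**What the plan says.** The Sample size section of the protocol article opens with "The sample size was calculated based on the expected reduction of incidence in MACE from pre- to post-treatment at 1 year". It takes from an earlier study that the MACE "incidence in high-risk patients with SCAD is about 10 % within 1 year", and continues "Assuming a MACE incidence reduction to 7 % following treatment with QXJYG added". It then adds "given a type I error rate of alpha = 0.05", sets power at 80%, and concludes that "the sample size for one arm needed to be 630", or 1,260 in total. An allowance for 20% dropout raises this to 1,512, and recruitment is set at 1,500.

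The design is fixed elsewhere in the article. Study objectives describes a parallel-group superiority trial against placebo. Randomization and treatment assignment says "Patients are randomized in a 1:1 ratio". Statistical approach compares the two groups by Kaplan-Meier curves, the log-rank test and Cox regression, analyses the primary outcome by intention to treat, and closes by stating that "all tests are two-tailed".

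**The concern.** All the inputs to the calculation are printed, and so is the result, but the result does not follow for the comparison that the trial makes. The section also describes the target as a change from before to after treatment, whereas the primary analysis compares events after randomisation between two concurrent arms.

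At stake is how the primary result is read. The article tells the reader that a true fall from 10% to 7% would be missed one time in five. If it would in fact be missed about half the time, a non-significant result could be taken as adequately powered evidence of no benefit when it is not.

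**Working it through.** **Inputs.** Placebo rate p1 = 0.10, QXJYG rate p2 = 0.07, alpha = 0.05 and power 80% (Sample size); two-sided tests (Statistical approach); 1:1 allocation (Randomization and treatment assignment). So d = 0.03, mean rate 0.085, z = 1.960 (two-sided) or 1.645 (one-sided) for alpha, and 0.8416 for power.

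**1. Reproducing 630.** A one-sample test of a proportion against a fixed value, two-sided, with null 7% and alternative 10%, gives

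n = [1.960·√(0.07·0.93) + 0.8416·√(0.10·0.90)]² / 0.03² = [1.960·0.2551 + 0.8416·0.3000]² / 0.0009 = 629.3, rounded up to 630.

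The match is exact. With null and alternative exchanged (null 10%, alternative 7%) the same formula gives 716. The article names no formula, so the link is an inference.

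**2. The comparison the trial makes.** Two independent proportions, pooled variance under the null:

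n per arm = [1.960·√(2·0.085·0.915) + 0.8416·√(0.0900 + 0.0651)]² / 0.03² = [1.960·0.3944 + 0.8416·0.3938]² / 0.0009 = 1,355.4, so 1,356 per arm and 2,712 in total. The ratio to the stated figure is 1,356/630 = 2.15.

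**3. Does the choice of method matter?** Two-sided n per arm under other standard methods:

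| Method | n per arm |
|---|---|
| Unpooled variance | 1,353 |
| Arcsine | 1,347 |
| Continuity-corrected | 1,422 |
| Log-rank, Schoenfeld (226 events) | about 1,329 |
| Log-rank, Freedman (232 events) | about 1,365 |

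The log-rank rows use HR = ln(0.93)/ln(0.90) = 0.689 and divide the events by 0.10 + 0.07. A one-sided test, pooled variance, still needs 1,068 per arm.

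**4. Power at the available sizes.** Power = Φ{[0.03·√n − 1.960·0.3944] / 0.3938}, with n per arm:

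| n per arm | Situation | z | Two-sided power |
|---|---|---|---|
| 630 | stated requirement | −0.051 | 48.0% |
| 750 | all 1,500 fully followed | 0.123 | 54.9% |
| 600 | 20% of 1,500 contribute nothing | −0.097 | 46.1% |

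With a one-sided test, 630 per arm gives 60.4%.

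**5. The same in events.** With 750 per arm and complete follow-up, 750·(0.10 + 0.07) = 127.5 events are expected against the 226 needed. Power by Schoenfeld is Φ{√127.5/2·|ln 0.689| − 1.960} = Φ(0.145), about 56%.

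**6. What 1,500 patients can detect.** With 750 per arm and a placebo rate of 10%, the step 4 formula (its variance terms recomputed for each rate) gives 79.3% power at a QXJYG rate of 6.1% and 80.4% at 6.05%. So 80% power corresponds to about 6.1%, a relative reduction of about 39% (3.9/10), against the 30% assumed (3/10).

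**The case against.** The strongest reply is that 630 is not arbitrary. A reader might infer that no standard formula yields it, but step 1 shows that a textbook two-sided formula does, and that it sits naturally with the section's before-and-after wording. This stands as a likely explanation. It does not justify the figure: a one-sample test treats one rate as known, whereas here both arms are samples and both contribute error.

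A second reply is that the Sample size section does not state sidedness. That is so, but Statistical approach does, and a one-sided test would still leave about 60% power.

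Third, the 46% figure can be called too harsh, and that objection stands in part. The plan is intention to treat with time-to-event methods and imputation, so patients who leave early still contribute follow-up time. At the planned 20% dropout, 46% is a lower bound, not the expected power.

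Two further inferences are tempting and should not be drawn. One is that a before-to-after change in MACE has no meaning. An incidence before and after treatment can be defined; it is simply not what this trial compares. The other is that a null result will inevitably be misread. The plan already provides hazard ratios with 95% confidence intervals, which would show the imprecision, so the documents support only that it could be misread.

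**Conclusion.** Wrong as written. For 10% versus 7% at two-sided 0.05, 80% power needs about 1,356 per arm, with a range of about 1,329 to 1,422 across methods. The stated 630 gives about 48%. The 1,500 patients to be recruited give about 55% with complete follow-up and not less than about 46% if 20% contribute no data.

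These figures take the article's 10% and 7% as the true rates, with equal arms. The conclusion does not depend on the choice of formula or on how dropout is handled, since 1,500 is well short of 2,712 even with no dropout. A reader might infer that the trial must enrol more patients or cannot be informative. Neither follows: the error lies in the stated power and sample size, and the planned confidence interval stays interpretable.

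**What to change.** In the Sample size section, replace the before-and-after description with the between-arm comparison and restate the figures. Suggested text: *With 1,500 patients randomised 1:1 and a two-sided significance level of 0.05, power to detect one-year MACE of 10% versus 7% is about 55% with complete follow-up, with a lower bound of about 46% if 20% contribute no data. Power of 80% is available for 10% versus about 6.1%. A non-significant result will be interpreted through the 95% confidence interval of the hazard ratio.*

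The cost is rewriting one paragraph and accepting a less favourable stated power. No extra enrolment, unblinding or change to the planned analysis is required. The change discloses the shortfall; it does not remove it.

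### The 20% dropout allowance is applied as 1,260 × 1.2 = 1,512 instead of 1,260 / 0.8 = 1,575, and the target is then cut to 1,500, so the plan misses its own required number

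*Protocol article*

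**What the plan says.** The Sample size section sets out a chain of figures. The control rate comes from an earlier study, in which MACE "incidence in high-risk patients with SCAD is about 10 % within 1 year". The effect is given as "Assuming a MACE incidence reduction to 7 % following treatment with QXJYG added". The error rates follow: "given a type I error rate of alpha = 0.05", with 80% power. From these the section derives 630 patients per arm, or 1,260 in total.

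It then allows for 20% dropout and states that "a total of 1512 patients needed to be allocated to reach the required number of patients for the efficacy analysis". The next sentence lowers the figure: "For convenience of randomization, we decided to recruit 1500 patients".

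Elsewhere the article says "Patients are randomized in a 1:1 ratio" (Randomization and treatment assignment) and "all tests are two-tailed" (Statistical approach).

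**The concern.** The stated purpose of the allowance is to have 1,260 patients left for the efficacy analysis after dropout. A dropout rate applies to the patients allocated, so the required number has to be divided by the retained fraction, 0.80. The plan multiplies by 1.20 instead, which gives a smaller number. It then sets recruitment 12 below that already understated figure.

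So even if 630 per arm is accepted without question, the recruited number does not deliver it at the plan's own dropout rate. A reader would credit the trial with a retention margin that it does not have. The faulty rule would also carry over into any recalculated sample size.

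**Working it through.** **Inputs**, all from the Sample size section unless noted: 630 per arm, 1,260 in total; dropout 20%; stated number to allocate 1,512; recruitment target 1,500; MACE 10% versus 7%; alpha 0.05, two-sided (Statistical approach); 1:1 allocation (Randomization and treatment assignment).

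**1. Reproduce the plan's figure.** n × (1 + d) = 1,260 × 1.20 = 1,512. This matches exactly, so the allowance was applied as a multiplier.

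**2. Number that meets the stated purpose.** n / (1 − d) = 1,260 / 0.80 = 1,575. This is 63 more than 1,512 and 75 more than 1,500.

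**3. What each number leaves, and the dropout it can absorb.**

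| Allocated | Left after 20% dropout | Against 1,260 | Largest dropout that still leaves 1,260 |
|---|---|---|---|
| 1,575 | 1,575 × 0.8 = 1,260 | 0 | 20.0% |
| 1,512 | 1,512 × 0.8 = 1,209.6 | about 50 short | 1 − 1,260/1,512 = 16.7% |
| 1,500 | 1,500 × 0.8 = 1,200 | 60 short (60/1,260 = 4.8%) | 1 − 1,260/1,500 = 16.0% |

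**4. Power cost on the plan's own scale.** Suppose 630 per arm did give 80% power. At 600 per arm the standardised effect shrinks by √(600/630) = 0.976. Power is then Φ(2.80 × 0.976 − 1.96) = Φ(0.77), about 78%. The loss is about 2 points.

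**5. Power on the stated rates.** For two proportions with n per arm,

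power = Φ{ [0.03 − 1.96 × √(2 × 0.085 × 0.915 / n)] / √[(0.10 × 0.90 + 0.07 × 0.93) / n] }.

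- n = 600: (0.03 − 1.96 × 0.01610) / 0.01608 = −0.097, power 46.1%.
- n = 630: (0.03 − 1.96 × 0.01571) / 0.01569 = −0.051, power 48.0%.

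The difference is again about 2 points. The distance from 80% has another cause: the same method needs 1,356 per arm for 80% power, so 630 does not follow from the stated inputs.

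**The case against.** The strongest reply is that patients who drop out are not lost to the primary analysis. The Statistical approach section analyses the primary outcome by intention to treat, with every randomised patient in the set and dropouts handled by imputation. It also uses Kaplan-Meier, log-rank and Cox methods, in which a patient contributes follow-up until censoring. If the 300 expected dropouts contribute an average fraction f of the year, 1,500 randomised patients carry roughly the information of 1,200 + 300f complete follow-ups. That reaches 1,260 at f = 0.20, or about 2.4 months. If dropout were spread evenly over the year, f = 0.5 and the equivalent is about 1,350. Both figures assume a roughly constant hazard, and the article gives no dropout timing.

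This stands as a comment on practical effect. It does not rescue the sample-size statement, which inflates specifically so that 1,260 remain after dropout and takes no credit for partial follow-up.

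Two further points are fair. The effect is small against the uncertainty in a control rate given only as approximate and a dropout rate that is itself a planning assumption. And the low absolute power, 46% to 48%, comes almost entirely from the figure of 630. Correcting dropout alone, to 1,575, would leave power near 48% with 630 per arm remaining.

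One could also read 20% as a fraction of completers, which would justify 1,512. That is not the natural meaning of a dropout rate, and 1,500 would still fall short of 1,512. The reduction to 1,500 is openly disclosed, but rounding for convenience should go up.

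**Conclusion.** The concern holds. At the plan's own 20% dropout, neither 1,512 nor 1,500 leaves the 1,260 patients it says it needs; 1,575 would. The target of 1,500 is 75 randomised patients below that number and leaves 1,200, a shortfall of 60. This rests on reading the dropout rate as a proportion of those allocated and on taking 1,260 as given.

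The error is modest by itself, at about 2 power points on either scale (80% to 78% if 630 were right; 48% to 46% on the stated rates with a two-sided 0.05 test). It still needs its own correction, because the statement is wrong as written and the multiplier would distort any revised calculation. With 1,356 per arm, for example, the total is 2,712 / 0.8 = 3,390, whereas multiplying by 1.2 gives only 3,255.

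**What to change.** In the Sample size section, delete the claim that 1,512 reaches the required number. State instead that 1,500 randomised patients leave 1,200 (600 per arm) at 20% dropout, or 1,260 if dropout is no more than 16%.

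Quote the power for that number: about 46% at 600 per arm for 10% versus 7% at two-sided 0.05, with 48% at 630 for comparison. Say that most of the gap from 80% comes from the 630 and only about 2 points from dropout. If the authors wish to take credit for partial follow-up under the intention-to-treat analysis, they should say so and give the dropout timing they assume. Any recalculated total should be divided by 0.8.

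The cost is one rewritten sentence, a less favourable stated figure, and no added enrolment.
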